#### Mediators

Mediators are health behaviours and lifestyle, and C reactive protein (as an indicator of systemic inflammation).

Health behaviours and lifestyle variables will include obesity (BMI>=30), alcohol intake (healthy versus unhealthy level; the former is defined as daily consumption of two drinks or fewer for men and women, according to the dietary guidelines in the UK - one drink contains 8g in the UK), smoking (healthy versus unhealthy levels; the former is defined as never smoked or smoking fewer than 100 cigarettes in life), physical activity (healthy versus unhealthy; the former is defined as 150 minutes of moderate-intensity physical activity weekly or 75 minutes of high-intensity physical activity weekly), poor appetite or overeating (Yes versus No), diet quality (healthy versus unhealthy level; the former is defined as meeting at least five out of the following ten dietary recommendations: 3 servings/day of fruit, 3 servings/day of vegetables, 3 servings/day of whole grains, ≥2 servings/week of (shell)fish, 2 servings/day of dairy, 2 servings/day of vegetable oils, ≤2 servings/day of refined grains, ≤1 serving/week of processed meats, ≤2 servings/week of unprocessed meats, and no sugar-sweetened beverages) (26, 27), trouble falling/staying asleep or sleeping too much (Yes versus No), ever addicted to any substance or behaviour (Yes versus No), and lifetime number of sexual partners.

The level of C-reactive protein (CRP) is used as a marker of bodily (systemic) inflammation and presented in mg/L.

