#### Covariates

Covariates are demographic variables: age, sex and ethnicity.

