#### Mediators

Mediators are health behaviours and lifestyle, and C reactive protein.

Health behaviours and lifestyle variables will include obesity (BMI>=30), alcohol intake (healthy versus unhealthy level; the former is defined as daily consumption of one drink or fewer for women and two drinks or fewer for men, according to the dietary guidelines in the US - one drink contains 14g of ethanol in the US), smoking (healthy versus unhealthy levels; the former is defined as never smoked or smoking fewer than 100 cigarettes in life), physical activity (healthy versus unhealthy; the former is defined as 150 minutes of moderate-intensity physical activity weekly or 75 minutes of high-intensity physical activity weekly), poor appetite or overeating (Yes versus No), diet quality (healthy versus unhealthy; the former is defined as the health eating index in the top two fifths of distribution), trouble falling/staying asleep or sleeping too much (Yes versus No), ever addicted to any substance or behaviour (Yes versus No), number of sexual partners in the past year, inconsistent condom use (“never” versus “occasionally” or “always”), toothbrushing (twice daily versus less than twice daily), dental flossing (once daily versus less than once daily) and dentist visiting (once every two years or more versus less than once every two years).

The level of CRP is used as a marker of bodily inflammation and presented in mg/L.

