#### Mediators

Mediators are health behaviours and lifestyle. No data is available in RELACHS on C reactive protein or other inflammatory markers.

Health behaviours and lifestyle variables will include being overweight or obese (having BMI above the 85th percentile and 95th percentile, respectively); alcohol consumption (never tried versus tried alcohol or consumed alcohol in the past week), smoking (never smoked versus ever tried or regular smoker), drug use (never tried versus tried drugs: cannabis, glue/solvents/gas, ecstasy, crack, heroin, amphetamines, LSD, cocaine and/or khat), physical activity (active versus inactive, exercising more or less than twice a week for an hour), diet as measured by the frequency of consumption of breakfast, crisps/savoury snacks, sweets, biscuits, fried food and fizzy drinks (“never”, “hardly ever”, “1-2 days a week” versus “3-4 days a week” or “daily”) as well as daily consumed portions of fruits and vegetables (5 or more portions daily versus less than 5 portions daily or none); dieting behaviour as measured by ever dieted to lose weight (Yes versus No) as well as present attempts to diet to lose or gain weight (Yes versus No); and tooth brushing (twice daily versus less than twice daily).

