#### Statistical analysis

Descriptive statistics will be used to summarise participants characteristics. For NHANES and RELACHS data, survey analysis procedures will be used to account for the sample weights, stratification and clustering of the complex sampling design to ensure representative estimates.

To answer the research questions on the presence of syndemic relationships, a structural equation modelling (SEM) technique will be utilised to conceptualise syndemic constructs and model complex relationships between directly observed and indirectly observed (latent) variables. The SEM technique has gained increasing popularity in syndemic research (30, 31). To use this technique, the following steps will be undertaken:

In step one, exploratory and confirmatory factor analyses will be used to identify the clustering nature and reduce the number of indicators (observed variables) under each theoretical construct. In step two, a SEM to predict premature mortality and all-cause hospitalisation, controlling for age, sex and ethnicity, will be run. Analysis will include identifying whether the indicators chosen to measure the latent constructs are acceptable. confirmatory factor analysis will be used to provide information on how indicator items measure underlying (latent) constructs. In step three of the analysis, SEM will be used to examine the direct and indirect relationships between the constructs. The goodness of fit (GoF) of the SEM model to the data will be assessed considering the indices of Comparative Fit Index (CFI) and Tucker-Lewis Index (TLI; where values >.90 indicate a good fit), root mean square error of approximation (RMSEA), and Standardised Root Mean Square Residual (SRMR; where value <.05 indicate a good fit). In step four, the synergistic (multiplicative) interactions between different latent constructs and measured variables will be tested using two-step estimation procedures (32).

To answer the question on whether syndemic relationships vary by age, sex and ethnicity, stratified analyses by age, sex and ethnicity will be performed.

Full Information Maximum Likelihood technique will be used as a pragmatic approach for data missing estimation for SEMs. This approach produces unbiased parameter estimates and standards errors (33). For UK BioBank and RELACHS datasets, stability of exposure data over time will be checked by calculating the intraclass correlation coefficients between baseline and follow up data.

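### Alcohol scoring in UK BioBank and NHANES places former drinkers in the healthy level, which can attenuate the paths into and out of the alcohol mediator

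*Protocol article*

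**What the plan says.** In the protocol article, the Mediators section for UK BioBank defines the healthy alcohol level as "daily consumption of two drinks or fewer for men and women, according to the dietary guidelines in the UK". The Mediators section for NHANES sets it at "daily consumption of one drink or fewer for women and two drinks or fewer for men". Both rules are upper limits on daily consumption. Neither sets a minimum, refers to drinking history or names a category for people who have stopped.

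The same sections define healthy smoking by lifetime history: "the former is defined as never smoked or smoking fewer than 100 cigarettes in life".

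These behaviours are mediators. Under Statistical analysis, step three states that "SEM will be used to examine the direct and indirect relationships between the constructs". Mental and physical multimorbidity are among those constructs. The adjustment set is short: "Covariates are demographic variables: age, sex and ethnicity". The only listed item that touches on past drinking is "ever addicted to any substance or behaviour (Yes versus No".

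**The concern.** Illness is a common reason to stop drinking, and illness is an exposure in this model. UK BioBank recruited people aged 40 to 69, so some participants will have stopped before baseline. Under the written rule they score healthy because they now drink nothing, and some of them are among the sickest people in that level.

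Both legs of the alcohol pathway are exposed. On the first leg, people with multimorbidity who have stopped drinking move into the healthy level, which weakens any positive association between multimorbidity and unhealthy drinking. On the second, former drinkers in poor health raise the death and hospitalisation risk of the level against which unhealthy drinking is compared. In NHANES, hospitalisation refers to the year before the survey, so a participant could be admitted, stop drinking and then be scored healthy with the outcome already present.

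Nothing else in the plan repairs this. Age, sex and ethnicity do not separate former from never drinkers. Full information maximum likelihood deals with missing values, and these values are recorded but pooled.

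**Working it through.** **Step 1: apply the written rules.** The documents give no figure to reproduce here, so the first check is to classify each drinking history. Consumption is read as consumption at assessment, which is the natural reading.

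| Drinking history | UK BioBank | NHANES |
|---|---|---|
| Never drank | healthy | healthy |
| Former drinker, now zero | healthy | healthy |
| Current, at or below the limit | healthy | healthy |
| Current, above the limit | unhealthy | unhealthy |

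The pooling of the second row with the first and third follows from the text and needs no assumption.

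**Step 2: direction and possible size on the alcohol-to-outcome leg.** Every input here is an assumption, since the documents supply none:
- f: former drinkers' share of the healthy level, 3% to 20%
- q: their risk relative to the rest of that level, 1.0 to 2.0
- R: the true ratio for unhealthy drinking against the rest of that level, 1.2 or 1.5

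Observed ratio = R / [(1 − f) + f × q]

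Loss on the log scale = 1 − ln(observed) / ln(R)

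| f | q | Divisor | Observed, R = 1.2 (loss) | Observed, R = 1.5 (loss) |
|---|---|---|---|---|
| any | 1.0 | 1.000 | 1.200 (0%) | 1.500 (0%) |
| 3% | 1.3 | 1.009 | 1.189 (5%) | 1.487 (2%) |
| 5% | 1.3 | 1.015 | 1.182 (8%) | 1.478 (4%) |
| 10% | 1.5 | 1.050 | 1.143 (27%) | 1.429 (12%) |
| 10% | 2.0 | 1.100 | 1.091 (52%) | 1.364 (24%) |
| 20% | 2.0 | 1.200 | 1.000 (100%) | 1.250 (45%) |

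Whenever q is above 1 the observed ratio falls. If former drinkers carry no extra risk, this leg is not biased.

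**Step 3: what the illustration leaves out.** It is a crude mixture of risks. The planned model also fits a direct path from multimorbidity to the outcome, which takes up part of the former drinkers' excess risk where that excess reflects the measured conditions. For that mechanism, the losses in the table are likely to be too high.

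**Step 4: the multimorbidity-to-alcohol leg.** The direct path to the outcome does not help here. Where illness causes stopping, the pooled coding records the change as a move to healthy drinking. The documents give nothing from which to size this.

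**The case against.** Several counter-arguments have force.

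- **Alcohol may not have its own path.** Step one of the analysis uses factor analysis to reduce the indicators under each construct. Alcohol is one of nine behaviour items listed for UK BioBank and thirteen for NHANES, and it may be one indicator among several or be dropped. This stands: the effect on any reported indirect effect could be smaller than a single-item calculation suggests.
- **The addiction item covers past problem drinking.** It does so only partly. It is not specific to alcohol and does not identify people who stopped because of illness.
- **Smoking.** A reader might infer that the smoking rule is wrong because it treats people who have stopped in the opposite way. The documents do not support this. Ever against never, with a 100-cigarette threshold, is a legitimate lifetime measure. With assumed ratios of 2.5 for current and 1.4 for former smokers, and 65% of ever-smokers having stopped, it gives 0.65 × 1.4 + 0.35 × 2.5 = 1.785, which is simply the ever-smoker ratio. Moving former smokers into the healthy level would bias the contrast too: if they made up 35% of that level, 2.5 / (0.65 + 0.35 × 1.4) = 2.19.
- **RELACHS.** A reader might see a contradiction in that cohort's lifetime rule, "alcohol consumption (never tried versus tried alcohol or consumed alcohol in the past week". The participants were recruited in Years 7 and 9, for whom that split is natural, and the article claims harmonisation only between NHANES and UK BioBank.

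None of these removes the alcohol problem itself.

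**Conclusion.** The point holds for alcohol in UK BioBank and NHANES. As written, the rules pool former drinkers with lifelong abstainers and light drinkers, and in a model with multimorbidity as an exposure this can attenuate both legs of the alcohol pathway. The coding follows from the text. The bias also requires that some participants stopped because of illness and, for the outcome leg, that former drinkers carry more risk than the rest of the healthy level.

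The size is unknown. The unadjusted illustration runs from 0% to 100% of the log ratio. Complete loss appears only at the corner of the assumed range (f = 20%, q = 2.0, R = 1.2), and the direct multimorbidity path would reduce these losses.

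A reader might infer that the indirect effect through alcohol changes sign. The documents do not support that. An indirect effect is the product of its two legs, so exactly one leg would have to reverse; if both did, the product would keep its sign. In the illustration the outcome ratio never falls below 1.00, and no figure in the documents shows that the first leg reverses. Attenuation is the supportable conclusion.

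**What to change.** Keep the stated intake limits. In the UK BioBank and NHANES Mediators sections, where past drinking is recorded, classify alcohol as never or within limit, former, and above limit. Enter it as one categorical variable. Separate factor indicators for the levels would be mutually exclusive and so dependent by construction.

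The article does not say whether past drinking is available in each database. Where it is not, add a sensitivity analysis that removes current non-drinkers from the healthy level, and state that this also removes lifelong abstainers.

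The cost is some recoding of questionnaire data, at least one more contrast on each path involving alcohol, and small former-drinker cells in some age or ethnic strata of the stratified analyses. Splitting smoking into never, former and current would add resolution, but it is an optional refinement and not a correction.

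### The physical activity cut-off makes no provision for combining moderate and high-intensity minutes, so as written some people above its implied threshold are coded unhealthy

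*Protocol article*

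**What the plan says.** The Mediators section under UK BioBank methods lists physical activity among the health behaviours and makes it binary: "physical activity (healthy versus unhealthy; the former is defined as 150 minutes" of moderate activity or the high-intensity alternative. The complete rule is that "the former is defined as 150 minutes of moderate-intensity physical activity weekly or 75 minutes of high-intensity physical activity weekly". The Mediators section under NHANES methods repeats it in the same words.

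Neither section has a clause for an equivalent combination or a weighted sum, and no other part of the article adds one. RELACHS uses a different rule, based on how often the young person exercises for an hour, and is not affected.

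The role of the variable is stated at the head of the UK BioBank section: "Mediators are health behaviours and lifestyle, and C reactive protein (as an indicator of systemic inflammation"). It is neither a syndemic construct nor an outcome.

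**The concern.** Two cut-offs that earn the same label imply an exchange rate between the intensities. An either/or rule then gives no credit to a person who falls short on each intensity but exceeds the standard on the two together. Because the variable is binary, everyone who meets neither cut-off goes into the unhealthy group, including people more active than some of those coded healthy.

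At stake is the quality of one mediator indicator. Step three of the Statistical analysis section estimates direct and indirect relationships between constructs. Placing sufficiently active people among the inactive may blur the paths into and out of this variable, and a larger cohort does not remove that error. The secondary aim compares strata of age, sex and ethnicity. If mixing of intensities differs between strata, the coding error would differ too, but the article gives nothing from which to judge whether it does.

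**Working it through.** **Inputs from the article** (Mediators, UK BioBank and NHANES)
- Moderate cut-off: "150 minutes of moderate-intensity physical activity weekly".
- High-intensity cut-off: "75 minutes of high-intensity physical activity weekly".
- Connector: either/or, with no combination clause.
- Scale: binary.

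The plan states no figure of its own to reproduce here.

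**Implied exchange.** 150/75 = 2, so one high-intensity minute stands for two moderate ones. The article does not say this; it follows from the two cut-offs sharing one label.

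**The two rules.** Let M be weekly moderate minutes and V weekly high-intensity minutes.
- As written: healthy if M ≥ 150 or V ≥ 75.
- Combined: healthy if M + 2V ≥ 150.

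| M | V | M + 2V | % of 150 | As written | Combined |
|---|---|---|---|---|---|
| 150 | 0 | 150 | 100 | healthy | healthy |
| 0 | 75 | 150 | 100 | healthy | healthy |
| 100 | 50 | 200 | 133 | unhealthy | healthy |
| 120 | 60 | 240 | 160 | unhealthy | healthy |
| 140 | 70 | 280 | 187 | unhealthy | healthy |
| 149 | 74 | 297 | 198 | unhealthy | healthy |
| 149 | 0 | 149 | 99 | unhealthy | unhealthy |

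The row 149 + 74 is the whole-minute extreme.

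**Direction of the coding error.** If M ≥ 150 or V ≥ 75, then M + 2V ≥ 150. Nobody coded healthy as written loses that code under the combined rule, so the difference is one-sided.

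**Dependence on 2:1.** Even at 1:1, 140 + 70 = 210 minutes, which is above 150 and still coded unhealthy. The misordering does not need the exact rate.

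**Size.** The article gives no distribution of minutes, so what follows is assumption. Weekly minutes were taken as exponential with mean M/V of 60/20, 90/30 and 120/40, joined by a Gaussian copula with correlation 0.3. The overall means were held fixed while the share with V = 0 was varied. The quantity is P(M < 150, V < 75, M + 2V ≥ 150), as a share of all participants.

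| Share doing no high-intensity activity | 60/20 | 90/30 | 120/40 |
|---|---|---|---|
| None | 11% | 15% | 16% |
| Half | 8% | 8% | 7% |
| 70% | 5% | 4% | 3% |

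In the first row the affected people are 12%, 20% and 25% of those coded unhealthy. Varying the correlation from 0 to 0.6 in that row keeps the share of all participants at about 10% to 16%. Across the nine cells, the median affected person has about 176 to 188 equivalent minutes. Most are therefore moderately above 150, and the 280-minute profile is a rare case.

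**The case against.** Five arguments can be made for leaving the rule alone.

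*The article may simply be brief.* It gives two benchmarks in parentheses and does not say that mixed minutes are discarded; the full protocol or the analysis code may combine them. That is possible, and it is why the point is confined to the definition as written. But the article does state a cut-off rule, and followed literally it misorders people. If the code already combines minutes, the published definition still needs correcting.

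*The 2:1 exchange is not in the document.* That is right: it is implied, and additivity is a further assumption. The misordering nevertheless survives at 1:1.

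*The size is assumed.* This stands. Exponential margins give everyone some high-intensity activity, which favours a large share. Allowing half or 70% of people to do none brings it down to single figures.

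*The effect on the results is not shown.* This also stands. A reader might infer that the indirect effect through activity is understated. The documents do not support that. Activity is one of nine behaviour items in UK BioBank and one of thirteen in NHANES. Step one of the Statistical analysis section uses factor analysis to reduce indicators, so the item may be dropped, or its error may go largely into its own loading and residual. Attenuation would be assured only if the error were unrelated to adversity and outcome, and nothing shows that.

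*Neither aim turns on this cut-off.* That is fair, since no construct or outcome uses it. It limits the importance of the point without removing it.

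**Conclusion.** The point holds as a minor defect in a stated coding rule. In both adult databases, people who mix intensities can exceed the implied threshold, in the extreme by almost double (297 against 150 equivalent minutes), and be coded unhealthy, while someone exactly at 150 moderate minutes is coded healthy. The error is one-sided relative to a combined rule.

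The share affected cannot be computed from the article. About 3% to 16% of participants is an illustrative range that rests on the assumed distributions and mainly on how many people do no high-intensity activity. The consequence is avoidable error in one behavioural mediator indicator, which may blur its paths. Neither the size nor the direction of any effect on the indirect estimates, nor any difference between strata, is established.

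**What to change.** In the Mediators sections for both UK BioBank and NHANES, define healthy activity as moderate minutes + 2 × high-intensity minutes ≥ 150 per week, or enter that sum as a continuous measure. State the 2:1 weighting as an assumption. If the analysis code already combines minutes, say so in the definition.

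The change needs no new data, because the current rule already requires minutes at each intensity. It costs a line of recoding per database and a sentence of text.

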#### Covariates

Covariates are demographic variables: age, sex and ethnicity.

### NHANES research questions

NHANES database will be used to answer the following research questions:

Are there syndemic relationships between social adversity and mental, physical and oral multimorbidity impacting mortality burden and all-cause hospitalisation?Do these syndemic relationships vary by age, sex and ethnicity?

### NHANES methods

#### Design and study population

The NHANES program is conducted in 2-year cycles by the Centers for Disease Control and Prevention. Data are obtained from self-reported questionnaires, clinical examinations and lab tests. Each cycle includes nearly 10,000 participants and is representative of the United States population across all age groups. In this project, NHANES cycles between 2009 and 2014 will be used due to required data availability and consistency. Attempts to harmonise variables’ selection across NHANES and UK BioBank databases are made.

#### Syndemic outcomes

The syndemic outcomes are premature mortality and all-cause hospitalisation. Mortality data are obtained from the National Death Index (available up to 31 December 2015). All-cause hospitalisation data are based on being hospitalised in the year preceding the survey.

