#### Syndemic outcomes

The syndemic outcomes are premature mortality and all-cause hospitalisation. Mortality data are obtained from the death register based on death certificates held within the NHS Digital (England and Wales) and the NHS Central Register (Scotland) between 01/01/2011 and 30/09/2021. All-cause hospitalisation data are obtained from the Hospital Episode Statistics data - Admitted Patient Care (England), Scottish Morbidity Records – General / Acute Inpatient and Day Case Admissions (Scotland), and Patient Episode Database (Wales) between 01/01/2011 and 28/02/2018.

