#### Covariates

Covariates are demographic variables: age, sex and ethnicity.

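### NHANES deaths accrue over about 1 to 7 years depending on survey date, but the stated mortality model includes no follow-up time, survey cycle or fixed horizon

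*Protocol article*

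**What the plan says.** All references are to the protocol article.

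- **NHANES, Design and study population.** "The NHANES program is conducted in 2-year cycles by the Centers for Disease Control and Prevention", and "NHANES cycles between 2009 and 2014 will be used due to required data availability and consistency". That makes three cycles.
- **NHANES, Syndemic outcomes.** "The syndemic outcomes are premature mortality and all-cause hospitalisation". For deaths, "Mortality data are obtained from the National Death Index (available up to 31 December 2015"; the same date applies to every cycle. Hospitalisation is taken from the year before the survey, so its window has the same length for everyone.
- **NHANES, Covariates.** "Covariates are demographic variables: age, sex and ethnicity".
- **Statistical analysis.** In step two, "a SEM to predict premature mortality and all-cause hospitalisation, controlling for age, sex and ethnicity, will be run". Fit is to be judged by CFI, TLI, RMSEA and SRMR. The section also covers survey weights, stratification and clustering, missing data and stratified analyses. It does not mention person-time, censoring, survey cycle or a common follow-up horizon.

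**The concern.** With staggered entry and one closing date, a participant recorded as alive may have been observed for one year or for seven. If the model sees only died or not died, those two records count the same, and the fitted risk of death belongs to no stated period.

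The second consequence is confounding. Time at risk is fixed by survey date, so any construct indicator that becomes more or less common between 2009 and 2014 is associated with time at risk and, through it, with the chance of a recorded death. The NHANES socioeconomic indicators include employment, income and health insurance, whose frequency could change over six years. Age, sex and ethnicity do not remove this, because they do not carry the survey date.

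**Working it through.** The article states no follow-up length, death rate or drift, so there is no figure of its own to reproduce. Dates come from the article. Rates and prevalences are assumptions and are marked as such.

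**1. Time at risk.** Formula: 31 December 2015 minus survey date. Exact survey dates are not given, so each cycle is taken to run from 1 January of its first year to 31 December of its second.

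| Cycle | Longest (years) | Shortest (years) | Midpoint (years) |
|---|---|---|---|
| 2009-10 | 7.0 | 5.0 | 6 |
| 2011-12 | 5.0 | 3.0 | 4 |
| 2013-14 | 3.0 | 1.0 | 2 |

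**2. Risk of recorded death.** Formula: 1 - exp(-rate x time), with a constant annual rate (assumed).

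- At 1% per year and 6, 4 and 2 years: 5.8%, 3.9% and 2.0%. The first cycle has 5.8/2.0 = about 2.9 times the risk of the last, for reasons unrelated to health.
- At the extremes, again at 1% per year: 6.8% over 7 years and 1.0% over 1 year, a ratio of 6.8. For rates from 0.5% to 5% per year the ratio runs from 6.9 down to 6.1.

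**3. Bias when an indicator drifts.** Assume cycles of equal size, uninsured prevalence of 20%, 17.5% and 15% across the three cycles, and no true effect on mortality.

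- Mean follow-up, uninsured: (0.20 x 6 + 0.175 x 4 + 0.15 x 2) / 0.525 = 2.2 / 0.525 = 4.19 years.
- Mean follow-up, insured: (0.80 x 6 + 0.825 x 4 + 0.85 x 2) / 2.475 = 9.8 / 2.475 = 3.96 years.
- Ratio: 4.19 / 3.96 = 1.058.
- Replacing years by the risks in step 2 gives 4.09% against 3.87%, a risk ratio of about 1.06 where the truth is 1.

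**4. A larger drift in the other direction.** Assume prevalence rises steadily from 20% to 30% over 2009-14, at 1% per year and with no true effect. The analytic risk ratio is 0.94. In a simulation of 600,000 participants, a logistic model without time at risk gave an odds ratio of 0.94 (standard error of the log odds ratio 0.016). A Poisson model with log person-time as offset gave 1.01. With a true rate ratio of 1.5 and the same drift, the two models gave 1.43 and 1.52.

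**5. No drift.** The analytic null risk ratio is 1.00. With a true rate ratio of 1.5, the logistic odds ratio was about 1.5. Unequal follow-up that is unrelated to the indicator leaves the direction and approximate size of an effect intact.

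**The case against.** The strongest reply is that the article never says death is modelled as a yes/no outcome. It names no link function, and in a survival-type SEM follow-up time belongs to the outcome and would not appear in a covariate list. A condensed article may leave that to a fuller plan. This stands in part: a survival model is not expressly excluded. But the article does fix the controls. It also treats mortality in the same sentence as a one-year hospitalisation indicator, and judges fit by covariance-structure indices that are not normally available for a survival outcome. Read as written, time at risk is left out.

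It is also fair to say that the bias needs drift, that the documents give no drift figure, and that the effect is small under plausible assumptions. That stands in full.

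A reader might infer three stronger points, which the documents do not support:

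- **That UK Biobank has the same defect.** It does not. Deaths there are counted in one common window, "between 01/01/2011 and 30/09/2021", about 10.75 years, which opens after recruitment (2006 to 2010) had ended.
- **That the two cohorts' mortality results cannot be compared.** No such comparison of coefficients is planned. Each dataset has its own research questions, and harmonisation is mentioned only for the selection of variables.
- **That the model would manufacture synergy.** Two factors that each double the hazard, with no interaction, do give an interaction odds ratio above 1 on the odds scale: (1 + S^2) / (S(1 + S)), where S is baseline survival. This is a matter of scale and arises equally when everyone has the same follow-up. At baseline risks of 2.0% to 5.8%, the illustrative NHANES levels above, it is only 1.01 to 1.03.

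**Conclusion.** The point holds for one outcome in one dataset: mortality in NHANES. The 1-to-7-year spread follows from the article's own dates, given the assumption about survey dates within cycles. The described model has nothing that accounts for it. The certain consequence is that the mortality outcome has no defined period, with roughly a threefold difference in risk between the first and last cycles at an assumed 1% per year. The conditional consequence is bias in any indicator that drifts across cycles: about 6% in either direction in the two assumed examples, and none without drift. This should be corrected before the models are fitted, but it does not by itself overturn the planned analysis. NHANES hospitalisation is unaffected.

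**What to change.** For the NHANES mortality model only:

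- **Preferred.** Treat death as a time-to-event outcome within the SEM, from survey date to death or 31 December 2015.
- **Alternative.** Keep a binary outcome with a complementary log-log link and enter the log of follow-up time as an offset. Follow-up here means the time available from survey to the closing date, not the time to death. The offset assumes a roughly constant hazard over the period.
- **Minimum.** Add survey cycle, or available follow-up time, as a covariate. Cycle removes confounding between cycles. It leaves up to two years' variation within each cycle and does not give the outcome a defined period.

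The article should state which is used. If a survival model is already intended, one sentence saying so would settle the matter.

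The cost is analysis wording and code. A survival outcome in a latent-variable model is slower to fit and yields fewer of the standard fit indices, so the stated fit criteria would need adapting for that model. The first two options also need individual survey dates or follow-up times, and the first needs times of death; the article does not say whether these are held. The cycle covariate needs nothing beyond the survey's own structure and costs almost nothing.
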